### Management of patients who develop comorbidities and those that become pregnant

Participants who develop TB, other opportunistic infections or comorbidities may require more frequent follow-ups than required by their dispensing interval. If they are in the 3MC or 6MCD arm, they will be considered unstable and are to be followed up at the facility hence transitioned off the study arm. These individuals will remain in observational follow-up but considered not retained for analyses. Providers will make these decisions and the study will track such outcomes. Frequency of ART dispensing will be determined based on national guidelines and clinician assessment. These events will be captured through patient routine records. Women who become pregnant whilst in the study will also require more frequent clinical visits for antenatal and postpartum care than required by their dispensing interval. If they are in the 3MC or 6MCD arm, they will return to be followed up at the facility. Frequency of ART dispensing will be determined based on national guidelines for ART in pregnancy and clinician assessment. These events will be captured through patient routine records. These individuals will remain in observational follow-up.

### Secondary outcomes

#### Time motion analysis

Regarding assessing the gains of facility decongestion, a pre- and 24-month post survey time-flow evaluation of patient waiting times will be conducted. These evaluations will be done over 5 days at each of the 30 facilities. These data will be collected using a study-specific time flow recording sheet for all patients visiting the facility during these 5 days. Mean total visit time, mean waiting time to be seen by the clinician and mean time for drugs to be dispensed will be calculated. Additionally, the monthly number of non-pregnant adults > 18 years ‘newly initiated on ART and receiving ART and provider-initiated counselling and testing at study facilities will be captured from facility records over the study duration to determine trends.

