## Abstract

**Background:**

Current World Health Organization (WHO) guidelines recommend early initiation of HIV positive patients on antiretroviral therapy (ART) irrespective of their clinical or immunological status known as the test and start approach. Lesotho, like many other countries introduced this approach in 2016 as a strategy to reach epidemic control. There will be rapidly growing number of HIV-infected individuals initiating treatment leading to practical challenges on health systems such as congestion, long waiting time for patients and limited time to provide quality services to patients. Differentiated models of ART delivery is an innovative solution that helps to increase access to care, while reducing the burden on existing health systems. Ultimately this model will help to achieve retention and viral suppression. We describe a demonstration study designed to evaluate a community-based differentiated model of multi-month dispensing (MMD) approaches of ART among stable HIV patients in Lesotho.

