Potential benefits for this approach includes (i) higher adherence to ART and retention in care, (ii) reduced per-patient cost of providing ART, by reducing the number of clinic visits required, (iii) decongestion of clinics to allow for increased capacity to manage patients newly diagnosed with HIV, those with infectious complications, treatment failure, and other co-morbidities and (iv) decreased waiting time and improved efficiency at clinics allowing for improved quality of care and patient satisfaction [7, 8].

Limited data are available from LMICs on multi-month scripting and dispensing and on studies using community-based models of care. A review of the literature reveals a lack of randomized studies of different ART dispensing intervals. An abstract presented at the Conference on Retroviruses and Opportunistic Infections, 2016 using Zambian data, suggested that requirements for monthly dispensing and/or systems that require multiple separate visits for refills and clinician evaluation can raise significant challenges for people living with HIV and result in treatment interruptions or complete disengagement from care [6].

This study’s primary objectives are (i) to determine if stable patients receiving 3 monthly dispensing of ART within CAGs have non-inferior retention in care and viral load suppression than stable ART patients receiving 3 monthly dispensing at health facilities after 12 and 24 months, (ii) 6 monthly dispensing of ART within the community from a health care worker have non-inferior retention in care than stable ART patients receiving 3 monthly dispensing at health facilities after 12 and 24 months and (iii) 6 monthly dispensing of ART within the community from a healthcare worker have non-inferior retention in care than stable ART patients receiving 3 monthly dispensing within CAGs after 12 and 24 months. The secondary objectives are to compare cost outcomes (cost per patient retained and cost per patient retained with viral suppression) between the three models, investigate the acceptability of 3 and 6 monthly community-based ART distribution among patients and service providers and to assess if there are measurable gains in clinic productivity realized following the introduction of community based MMD of ART.

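### The decongestion outcome is worded as before-after change with no between-arm contrast stated, although baseline and 24-month times are collected at all 30 randomised facilities

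*Protocol article*

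**What the plan says.** The decongestion outcome appears in three places in the protocol article.

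- **Objective (Background, last paragraph).** A secondary objective is "to assess if there are measurable gains in clinic productivity realized following the introduction of community based MMD of ART". The same sentence words the cost objective as a comparison of the three models.
- **Outcome list (Study measures and outcomes).** Cost-effectiveness is listed as a comparison between arms. Decongestion, the third item, is listed as measurable gains, without that phrase.
- **Method (Time motion analysis).** The section says that "a pre- and 24-month post survey time-flow evaluation of patient waiting times will be conducted". On coverage: "These evaluations will be done over 5 days at each of the 30 facilities", with times recorded "for all patients visiting the facility during these 5 days". On summaries: "Mean total visit time, mean waiting time to be seen by the clinician and mean time for drugs to be dispensed will be calculated". Monthly numbers of adults starting ART, receiving ART and being tested "will be captured from facility records over the study duration to determine trends".

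The only between-arm analysis in the article (Statistical analysis, power and sample size considerations) is a GEE model giving risk differences and risk ratios for each intervention arm against control.

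**The concern.** A change from before to after is attributable to community dispensing only if nothing else moves waiting times over the same 24 months. The article itself names two things that would.

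- **Growth in caseload.** The Abstract says: "There will be rapidly growing number of HIV-infected individuals initiating treatment leading to practical challenges on health systems such as congestion, long waiting time". The time-flow survey covers every attender, not only trial participants, so this growth enters the measured times directly.
- **A change in the control arm.** The section on the three-month facility model moves control visits to every 90 days in place of the standard interval, and the Background describes current dispensing as monthly. A before-after change in any arm therefore mixes longer dispensing intervals with whatever community delivery adds, and control facilities' own change is not a trend free of intervention.

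At stake is the interpretation of a secondary objective. A real gain could be hidden by rising attendance, or a fall in waiting time that would have happened anyway could be credited to the community models.

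**Working it through.** The article gives no effect size, standard deviation, trend or power for waiting times; its sample size is for retention only. There is no stated figure to reproduce, so the check is of wording first, then two illustrations on assumed values.

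**1. Which contrast does the text state?** The objective speaks of gains after introduction, the outcome list omits the arms for this item, and the method gives two survey times, three means and trends. No section names a comparison of arms for waiting times. The GEE model does not fill the gap as written, because risk differences and risk ratios are not measures for mean minutes.

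**2. What do the planned data allow?** Times are collected before the study and at 24 months in all 30 facilities, and Study design puts 10 facilities in each arm. Each community arm can be compared with 3MF, 10 facilities against 10, with a baseline value for every facility.

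**3. How far can a trend shift a before-after change?** Assume a true 20% reduction from community dispensing and a background trend g shared by all arms. Apparent change = (1 + g) × (1 − 0.20) − 1.

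| Assumed trend g | Apparent before-after change |
|---|---|
| −10% | 0.90 × 0.80 − 1 = −28% |
| +20% | 1.20 × 0.80 − 1 = −4% |
| +30% | 1.30 × 0.80 − 1 = +4% |

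The true gain disappears entirely at g = 1/0.80 − 1 = +25%. Between arms at 24 months, the ratio of community to control is (1 + g) × 0.80 / (1 + g) = 0.80 for every g. In minutes, the difference is 20% of the control arm's 24-month mean, so its sign does not depend on g, although its size scales with that mean.

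**4. How often would a before-after test find a change with no true effect?** Take facility-level changes, with an assumed drift of d standard deviations of that change and a two-sided 5% one-sample t test on k facilities. The noncentrality is d√k. The column for k = 20 supposes that both community arms are pooled, which the article does not say.

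| Assumed drift d | k = 10: d√k, rejection | k = 20: d√k, rejection |
|---|---|---|
| 0.25 | 0.79, 11% | 1.12, 19% |
| 0.5 | 1.58, 29% | 2.24, 57% |
| 1.0 | 3.16, 80% | 4.47, 99% |

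Comparing the changes between arms, 10 facilities against 10, a common drift cancels: the noncentrality is 0 and rejection stays at 5%.

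**The case against.** The strongest reply is that the Time motion analysis section fixes when, where and on whom times are measured and which means are calculated, but no contrast. Two surveys are also exactly what a baseline-adjusted comparison of arms needs. The context supports this: under Qualitative data collection, where only the community arms are of interest, the article restricts itself to those 20 facilities, whereas the time-flow survey includes the 10 control facilities at both times. The article also condenses a fuller protocol, and the model for a secondary outcome is commonly left to the analysis plan. Finally, every trend and effect size above is assumed.

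Most of this stands. A reader might infer that the trial has discarded its randomised comparison, or that it will mistake secular change for an effect. The document supports neither: it does not pool the arms or exclude the controls, and the data keep the comparison available.

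Two things remain. The contrast belongs to the objective, which the article does state, and states as change over time; an analysis plan that followed that wording could properly report before-after means alone. Nor do the monthly counts settle the matter. They document caseload growth but do not remove it from the mean times. The Background also lists capacity for newly diagnosed patients among the expected benefits, so the counts may themselves respond to the intervention.

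It is also fair to say that a comparison with 3MF estimates something different from the total gain since introduction. That must be stated alongside the contrast.

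**Conclusion.** The point holds as one of wording and choice of contrast. Objective, outcome and method frame decongestion as pre/post change, no between-arm comparison is stated for it, and the planned data would support one. Taken as written, the before-after change can be confounded by the growth that the article expects and by the control arm's own change of interval.

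The size cannot be given from the document. Under the assumed values, a true 20% reduction could appear as anything from −28% to +4%, and a drift of half a standard deviation would produce a false finding 29% of the time with 10 facilities. These figures show how the bias works; they do not predict it. The between-arm contrast removes only a trend common to the arms; randomisation of facilities is the reason to expect one, subject to chance imbalance with 10 per arm. The outcome is secondary and nothing here touches the retention analysis.

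**What to change.** State in the objective and in the Time motion analysis section, or in the analysis plan:

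- For each of the three time measures, 24-month facility means are compared between arms, each community arm against 3MF, with the facility as the unit, adjusted for the facility's baseline mean and the rural/urban stratum, and reported as a difference with a 95% confidence interval.
- Trends in the monthly counts are compared by arm (an arm-by-time term).
- Before-after means are reported within each arm as description only.
- The contrast with 3MF estimates the gain over 3-monthly facility dispensing. For 3MC this is community delivery at the same interval; for 6MCD it is community delivery plus the longer interval. It does not estimate the gain over earlier care.

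The cost is a few sentences and a short analysis, with no new data. The drawback is precision: with 10 facilities per arm the interval will be wide, and wider than a before-after interval that ignores clustering.

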#### Feasibility of MMD of ART in CAGs and community distribution

The feasibility assessment and analysis will include technical, resource and structural aspects. Data will be collected prospectively on study-specific forms at the beginning of the study,12 and 24 months. Before the study activates, facilities will be assessed on their ability to do essential medicine quantifications and forecasting. Each facility’s ability to generate quality data (measured by pre-determined criteria) and to ensure constant supply of medicines to the study participants through efficient ordering and delivery processes will be assessed. Feasibility will also be analysed by the ability of facilities to source adequate storage facilities, utilize efficient transportation systems and the turnaround time for ordering of medicines. For those within CAGs, attendance registers will be used to get a sense of individuals participating rates.

#### Qualitative data collection

Qualitative data will be collected at baseline, 12 and 24 months. Primarily, it will be to explore the acceptability of CAGs and community ART distribution by patients and service providers, patient satisfaction and improvement in quality of care at the facilities. Focus group discussions (FGD) with study participants in the 3MC and 6MCD arms will be held to explore the range of issues regarding acceptability of CAGs and community ART distribution. Each facility will conduct one FGD with up to 10 study participants at each data collection point. A total of 20 FGD will be held at each data collection point. Key informant interviews (KII) will be done with service providers including the facility manager and healthcare workers. Each of the 20 facilities will have a key informant selected for the interviews. A total of 20 KII will be collected for the study at each data collection point.

This will give a total of 40 data points for analysis for the qualitative research. It is hoped that a saturation of findings will be reached by this sample size. Data will be collected by trained facilitators in each FGD using piloted discussion and interview guides for the FGD and the KII respectively. Each FGD will be conducted by 1 facilitator and 1 note taker, whilst KII will be conducted by 1 interviewer. Data collection for FGD will be in Sesotho and it is assumed that all service providers are conversant in English. All qualitative data will be recorded, transcribed, translated to English and coded. All participant in FGDs and KIIs will be required to sign consent to participate and to be recorded.

#### Costing and cost-effectiveness

A micro-costing approach, also known as the bottom-up method will be used. This will allow the tracking of every input in carrying out the study interventions. However, this approach will be supplemented by a macro-costing approach of fixed costs such as infrastructure, building, equipment, utilities etc. To ascertain the cost to provider, we will estimate the fixed and variable costs to care. Fixed cost to patients will include (i) equipment and vehicles (ii) building and Infrastructure and (iii) administration costs and other above point-of-care costs. As for variable costs, these will include but not limited (i) outpatient care (type and number of visits) (ii) Inpatient care (number of bed days in care) (iii) other services (ARTs, laboratory tests, non-ART drugs, consumables etc.).

Patient level costing, also known as direct non-medical costs will also be collected. These costs are borne by either the patient or relatives of the patient to improve the care towards the patient. This study intervention is expected to result in patient level benefits such as reduced cost for care seeking, productivity benefits due to reduced time spent seeking care and informal care effects. Data to assess patient level costs will be collected from a randomly selected sub-sample of patients from each arm. Costing outcomes will include:(i)average cost per patient retained in care and virally suppressed at 12 and 24 months (cost per patient retained)(ii)annual cost per patient in each cohort/arm (per patient year cost)(iii)cost-effectiveness of the intervention arms will be compared with respect to retention in care and viral suppression.

#### Safety assessment, monitoring, and reporting

Participant safety will be carefully assessed, monitored and reported at multiple levels throughout this study. Site investigators, clinical management committee, and an independent data and safety monitoring board will be set up to continuously assess, monitor and report on all safety related matters. All protocol deviations, or unintended consequences/adverse events related to the study and its design will be recorded and appropriately addressed.

#### Statistical analysis, power and sample size considerations

Descriptive data of the study population stratified by treatment arm will presented as medians and interquartile ranges for continuous variables and proportions for categorical variables.

Our analysis will use an intention-to-treat approach in which generalized estimating equations (GEE) will be computed to estimate risk differences and risk ratios and associated 95% confidence interval for the effect of each intervention arm compared to the control (Patients receiving 3 monthly ART supply at facilities), specifying for clustering by facility. A small cluster size variance correction will be used. Should we identify any baseline imbalances between study arms, we will adjust for these through multivariable regression models and report adjusted effect measures and corresponding 95% confidence intervals.

Qualitative analysis will be employed in this study to ascertain feasibility, acceptability of CAGs and community ART distributions by patients and service providers. Summative content analysis which involves counting and comparisons of keywords or content, followed by the interpretation of the underlying context will be conducted. The data will be further analysed for emerging key themes and the findings will be interpreted based on each research question. Quotes will also be extracted for each of the themes that emerge from the data. It is anticipated that MMD will reduce both facility and patient costs of treatment and that it will be cost-saving compared to standard of care. For facilities, fewer clinic visits by patients should save the time of providers and support staff. For patients, fewer clinic visits are expected to reduce the costs of travel and to save time. The study will estimate differences in both provider and patient costs. Cost-effectiveness will be estimated as the average cost per successful outcome (patient retained at 12 and 24 months).

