### Study measures and outcomes (data collection matrix)

The schedule of visits and evaluations to be done are outlined see Additional file 1. The primary outcomes to be compared between arms for this study are retention and VL suppression. Secondary outcomes will include the following (i) comparisons in cost effectiveness between arms, (ii) acceptability of models to patients and service providers and (iii) measurable gains in decongestion in facilities through motion time assessments/analysis.

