### Sample size estimate

Sample sizes were determined for a cluster randomized non-inferiority trial with retention in care at 12 months as the primary outcome. A total of 30 study sites will be available for randomization, with three study arms, 10 clusters per arm, and participant enrolment numbers will be assumed to be equal at each site. The probability of patient attrition 12 months after study enrolment is assumed to be 5%. An intra-cluster correlation coefficient of 0.01 for patient retention/attrition amongst stable ART patients is assumed from a previous cluster randomized trial including stable ART patients [9]. The non-inferiority limit is specified as 3.25%. Assuming α = 0.05, power of 85%, and using a one-sided Z-test (un-pooled) statistic, approximately 192 enrolled participants per facility will be required with a total sample size of 5760 participants, representing 1920 participants per arm.

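### The third primary objective (6-monthly community supply non-inferior to CAG supply) has no matching contrast in the stated analysis, which compares each intervention arm with control

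*Protocol article*

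**What the plan says.** In the protocol article, the end of the Background sets out the objectives. The list opens "This study’s primary objectives are (i) to determine if stable patients receiving 3 monthly dispensing of ART within CAGs" and has three items. The third is that 6-monthly community dispensing by a health care worker should "have non-inferior retention in care than stable ART patients receiving 3 monthly dispensing within CAGs after 12 and 24 months". It stands in the same list as the two comparisons with facility supply and has the same primary status.

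The section Statistical analysis, power and sample size considerations describes the effectiveness analysis. It says that "generalized estimating equations (GEE) will be computed to estimate risk differences and risk ratios and associated 95% confidence interval", and it fixes the comparisons as "for the effect of each intervention arm compared to the control". A bracket straight after these words defines control as the 3-monthly facility supply arm.

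Three other places bear on the point:
- Study measures and outcomes says "The primary outcomes to be compared between arms for this study are retention and VL suppression" and names no pair of arms.
- Costing and cost-effectiveness provides for comparing the intervention arms, but only on cost-effectiveness.
- Sample size estimate sizes one two-arm non-inferiority comparison and does not say which pair: "Assuming α = 0.05, power of 85%, and using a one-sided Z-test (un-pooled) statistic".

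**The concern.** Two statements in the same document do not match. The objectives require three pairwise non-inferiority comparisons, and the analysis section names two. The article is not silent on which comparisons will be made. It says which, and one primary comparison is not among them.

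An analyst who follows the analysis section as written will produce no estimate, interval or non-inferiority conclusion for objective (iii). If the contrast is added later, whether the 3.25-point margin applies to it would be decided after the fact. Nor can a reader recover the interval properly from the two planned contrasts. Subtracting them gives the point estimate, but both share the 3MF arm, so the standard error of their difference needs a covariance that would not normally be reported.

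**Working it through.** **Matching objectives to contrasts**

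| Primary objective (Background) | Contrast needed | Named in the analysis section? |
|---|---|---|
| (i) | 3MC vs 3MF | Yes |
| (ii) | 6MCD vs 3MF | Yes |
| (iii) | 6MCD vs 3MC | No |

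No other section of the article specifies an effect estimate or a non-inferiority test for 6MCD vs 3MC.

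**Does the design support the missing contrast?**

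Inputs, all from Sample size estimate: attrition 5% at 12 months, taken here as equal in all arms; ICC 0.01; 10 clusters per arm; 192 participants per cluster (1920 per arm); margin 3.25 percentage points; one-sided α 0.05; power 85%; unpooled Z test.

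1. *Reproduce the plan's figure.* Under individual randomisation, n per arm = 2 × 0.05 × 0.95 × (1.645 + 1.036)² / 0.0325² ≈ 647.
2. Design effect = 1 + (192 − 1) × 0.01 = 2.91.
3. 647 × 2.91 ≈ 1883 per arm, against 1920 stated. The plan's number reproduces to within about 2%. A one-sided α of 0.025 would give 2351 and does not reproduce it.
4. *Standard error of any pairwise risk difference.* √(2 × 0.05 × 0.95 × 2.91 / 1920) = √(0.27645 / 1920) ≈ 0.0120, or 1.20 points. The 95% CI half-width is 1.96 × 1.20 ≈ 2.35 points.
5. *Power for 6MCD vs 3MC with no true difference.* Φ(0.0325 / 0.0120 − 1.645) = Φ(1.06) ≈ 85.6%. The arms are equal in size and in assumed attrition, so this is also the power of each control contrast.
6. *Sensitivity.* With a t reference on 18 degrees of freedom, power is 83.1%. If the limit of a two-sided 95% CI is used (one-sided 0.025), it is 77.3% by the Z test. Both changes affect all three contrasts alike.

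**Why the contrast should come from the same model**

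If the two control contrasts were treated as independent, the half-width for 6MCD minus 3MC would be 2.35 × √2 ≈ 3.33 points instead of 2.35. As 3.33 exceeds the 3.25-point margin, even an observed difference of zero would not show non-inferiority on that interval. The direct model contrast avoids this.

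**The case against.** The best defence is that this is an incomplete sentence in a condensed article. The analysis section does not say that comparisons are made with control alone, the outcomes section speaks of comparing arms in general, and the sample size is generic to any pair. A three-arm GEE yields 6MCD minus 3MC directly, and an analysis plan that is not shown may already include it. Much of this stands, and it limits the seriousness of the point. It does not remove the mismatch: the article does state its comparisons, and a plan that tested objective (iii) would go beyond that wording.

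A reader might infer more than the document supports, in four ways:
- *That the trial cannot answer objective (iii), or is too small for it.* The calculation shows otherwise.
- *That two margins chain, so that 6MCD could pass while 3.25 + 3.25 = 6.5 points worse than 3MF.* Objective (ii) compares 6MCD with 3MF directly and the analysis section covers it, so such a deficit would be tested and reported in the same trial.
- *That the stated 85% should be set against the chance that all three contrasts succeed.* The article states no such success rule. It lists three separate objectives.
- *That objective (iii) must be gated on 3MC first being non-inferior to 3MF.* The article states no testing order that could be contradicted, and order is commonly left to the analysis plan. Gating also has a price: at the planning values, the chance of passing both tests is about 72% at one-sided 0.05, against about 86% ungated.

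**Conclusion.** The point holds as a conflict between the objectives and the stated analysis: one of three declared primary comparisons, 6MCD vs 3MC on retention, has no planned effect estimate. It should be corrected, but it is a matter of specification and does not show a flaw in the design or the sample size.

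The power of about 86% rests on 5% attrition in every arm, ICC 0.01, equal clusters of 192, a one-sided Z test at 0.05 and the 3.25-point margin applying to this pair. It concerns 12 months only, because the article gives no planning value for 24 months. The textual mismatch depends on none of these assumptions.

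Non-inferiority of 6MCD to 3MC says little by itself if 3MC does poorly against 3MF. That calls for reading the three contrasts together and does not make any particular testing order obligatory.

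**What to change.** In the analysis section, add the 6MCD minus 3MC risk difference in retention, with its confidence interval, at 12 and 24 months. Estimate it from the same three-arm GEE with the same handling of clustering and the same small-sample correction. State that it is judged against the 3.25-point margin, and that it is interpreted beside the direct 6MCD vs 3MF and 3MC vs 3MF contrasts. If the investigators do not intend to test this pair, they should stop calling objective (iii) primary.

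The cost is one further contrast from a model already planned and a sentence or two of text, with no extra patients or data. Trial status reports that enrolment is still under way, so on the article's own account the change can be made before outcome results could influence it.

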### Study design

The study will be a pragmatic, three arm, parallel, cluster-randomized non-inferiority design. The thirty facilities (clusters) will be randomly assigned to three arms (Fig. 1) with patients receiving (i) 3MF- 3 monthly ART supply at facilities (Control), (ii) 3MC - 3 monthly ART supply through community ART groups (CAGs) and (iii) 6MCD - 6 monthly ART supply through community distribution points (CAD). Included facilities will be randomized, with stratification by whether the facility is in a rural or urban setting according to the Lesotho Bureau of Statistics’ data. After this process, each arm will, contain 10 facilities.

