### Entry visit/baseline procedures

For those that enrol, the following detailed data will be collected and recorded from clinical and medical record review: HIV history, HIV-related medications, date of ART initiation, prior adherence/VL data, socio-demographic data including age, gender, level of education, estimated distance and time to travel to clinic, employment status, disclosure status and marital status. Costing data (patient cost data) including travel costs to clinic, opportunity cost of time spent on medication pickup visits etc., will be recorded.

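### Facilities are randomised within rural/urban strata, but the stated analysis names no stratum term, ties adjustment to imbalances seen in the data, and does not say which result decides non-inferiority

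*Protocol article*

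**What the plan says.** **Randomisation.** Under Study design: "Included facilities will be randomized, with stratification by whether the facility is in a rural or urban setting". Each of the three arms receives 10 facilities.

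**Model.** Under Statistical analysis, power and sample size considerations, GEE will be used "to estimate risk differences and risk ratios and associated 95% confidence interval" for each intervention arm against control, "specifying for clustering by facility". The section adds: "A small cluster size variance correction will be used". It names neither the rural/urban stratum nor any pre-specified covariate.

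**Adjustment rule.** The next sentence reads "Should we identify any baseline imbalances between study arms, we will adjust for these through multivariable regression models", after which the authors will "report adjusted effect measures and corresponding 95% confidence intervals". It gives no criterion for imbalance, no list of candidate variables, and no statement of which result is compared with the margin.

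**Available covariates.** Under Entry visit/baseline procedures, the data collected include HIV and ART history, age, gender, education, and "estimated distance and time to travel to clinic, employment status, disclosure status and marital status".

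**The concern.** There are two linked problems.

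First, the result that decides non-inferiority is not identified. The plan yields one set of estimates and, if an imbalance is noticed, a second. With 10 facilities per arm and about ten baseline items, some imbalance is likely. The covariates in the second set would then be chosen after seeing the data. If the two sets fall on opposite sides of 3.25 points, the text does not settle which one counts.

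Second, the trigger works against the design. Rural/urban setting is the one factor that the randomisation controls, so it is the factor least likely to look imbalanced and be adjusted for. If it predicts attrition and is left out, its variance stays in the standard error although stratification has already removed it from the comparison between arms. The interval is then wider than the design warrants.

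**Working it through.** **Inputs from the article (Sample size estimate).** 10 facilities per arm, m = 192 per facility, attrition p = 0.05 in both arms, ICC 0.01, margin 0.0325, one-sided alpha 0.05, power 85%.

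**Inputs that are assumptions.** The urban/rural gap in attrition (d, taken as 0 to 3 points) and the share of facilities in each stratum (5/5 per arm, then 2/8). The article gives neither.

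**Step 1: reproduce the stated sample size.**
- Individually randomised: n = 2 × 0.05 × 0.95 × (1.645 + 1.036)² / 0.0325² ≈ 647 per arm.
- Design effect: 1 + 191 × 0.01 = 2.91.
- Product: 646.6 × 2.91 ≈ 1,882 per arm, against 1,920 stated.
- SE at 1,920 per arm: √(2 × 0.0475 × 2.91 / 1920) = 0.0120.
- Power (z, one-sided 0.05): Φ(0.0325/0.0120 − 1.645) = 85.6%.

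The stated figure holds. It makes no use of strata.

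**Step 2: how much variance the stratum could carry.**
- Between-facility variance: 0.01 × 0.0475 = 0.000475.
- Within-facility variance of a facility mean: 0.99 × 0.0475 / 192 = 0.000245.
- Total variance of a facility mean: 0.000720.
- With a share q of facilities in one stratum, the stratum contributes d² × q(1 − q). Including it multiplies the SE by √(1 − share of total).

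| Gap d (5/5 split) | Stratum variance | Share of facility-mean variance | SE ratio, with v without |
|---|---|---|---|
| 1 point | 0.000025 | 3.5% | 0.98 |
| 2 points | 0.000100 | 13.9% | 0.93 |
| 3 points | 0.000225 | 31.3% | 0.83 |

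**Step 3: power and error by simulation.** Beta-binomial facility outcomes, 10 v 10 facilities, 192 each, total ICC held at 0.01, 20,000 trials per setting for the 0.05 column. Facility-level linear analysis without the stratum (t, 18 df) and with it (t, 17 df). True difference 0 for power.

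| Gap (5/5 split) | Power at one-sided 0.025, without v with | Power at one-sided 0.05, without v with |
|---|---|---|
| 0 points | 73% v 73% | 83.4% v 83.1% |
| 1 point | 74% v 74% | 83.9% v 84.5% |
| 2 points | 74% v 79% | 84.2% v 87.3% |
| 3 points | 76% v 87% | 86.4% v 92.7% |

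The 0.025 column corresponds to the 95% interval in the analysis section. The 0.05 column corresponds to the sample size section. With 2 urban and 8 rural facilities per arm and a 2-point gap, the 0.025 figures are 73% v 77%.

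**Step 4: calibration.** With the true difference set at the margin, the error rate without the stratum at nominal 2.5% is 1.7% (2-point gap) and 0.9% (3-point gap). At nominal 5% it is 3.9% and 2.4%, against 5.0% and 4.8% with the stratum. At a 3-point gap the mean estimated SE without the stratum is 0.0120, while the estimator's actual standard deviation is 0.0100. The estimate itself is no more variable; only its reported SE is too large.

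**Step 5: how often the trigger would fire.** Suppose ten independent baseline items and an imbalance criterion of p < 0.2 (both assumed). The chance of at least one flag is 1 − 0.8¹⁰ = 0.89. This illustrates why the rule is likely to come into play; the article sets no criterion.

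**The case against.** **The stratum point rests partly on silence.** An article paragraph commonly leaves model terms to the full protocol or SAP. A reader might infer that the trial has decided to exclude the stratum. The text does not say so; it only fails to name the stratum where it names facility clustering. This stands, and it limits the stratum half of the point. It does not reach the imbalance rule, which is stated outright and which a later plan would have to override.

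**The precision figures are conditional.** A 3-point gap would mean that one binary factor explains 0.000225/0.000475 = 47% of the assumed between-facility variance; at 2 points it is 21%. Nothing in the article shows a gap of either size. This also stands.

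**Planned power is not eroded.** A reader might infer from the tables that leaving out the stratum costs the trial its planned power. It does not: power without the stratum stays at or slightly above its no-gap level, and what is lost is a gain the design makes available. The lower level in the 0.025 column reflects the alpha, which is a separate matter. The error is also in the safe direction, so no false claim of non-inferiority follows from omitting the stratum.

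**The primary estimate is not shown to be data-driven.** A reader might infer that the adjusted result replaces the unadjusted one. The article does not say that. The GEE risk differences come first and the adjusted measures follow conditionally. What can be said is that the deciding result is not named.

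**Conclusion.** The point holds in a limited form. The article stratifies randomisation by rural/urban setting, names only facility clustering in the analysis, lets observed imbalance choose the covariates, and does not say which result is compared with 3.25 points. That rest on the text alone and needs no assumption.

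The precision at stake is nil to about 1 power point for an urban/rural gap of 0 to 1 point, about 5 points for a 2-point gap and about 11 for a 3-point gap. These figures are at one-sided 0.025 and assume 5 urban and 5 rural facilities per arm and a total ICC of 0.01. They are smaller with an uneven split and at one-sided 0.05 (about 3 and 6 points at gaps of 2 and 3). The correction is worth making because it is nearly free, not because the trial's validity depends on it.

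**What to change.** In the statistical analysis section:

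1. Include the rural/urban randomisation stratum in the primary GEE.
2. If further covariates are wanted, choose a short list from those collected at entry and fix it before outcome data are seen. Which ones is for the trial team to justify; the article does not show which predict attrition.
3. Name the risk difference from that model as the result compared with the 3.25-point margin.
4. Relabel adjustment for imbalances found afterwards as a sensitivity analysis.

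If the full protocol or SAP already does this, the article's imbalance sentence should be brought into line with it.

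**Cost.** Analysis wording, one degree of freedom for the stratum and any for the chosen covariates. With 20 facilities in each two-arm comparison, that is a reason to keep the list short. There is no new data collection and no change to the sample size.
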